#### Secondary study parameter(s)

The mean daily postoperative pain scores over the 1-week period will be compared between the groups using linear mixed-effects regression with a random intercept and slope to account for multiple measurements over time within patients. Covariance between random effects will be estimated using an unstructured covariance matrix. Correlation between measurements over time will be modeled using a first order autoregressive structure. Both differences in average pain level over time and differences in trend across time will be assessed.

Time to opioid cessation will be analyzed with the Kaplan-Meier method and compared using the log-rank test.

Mean pain intensity and pain interference at 2, 6, and 12 months will be compared using linear mixed-effects regression with regards to group differences and time course.

Quality of life at 6 and 12 months will be compared between groups using the independent-samples *t*-test.

The effect of surgery on QST and CPM parameters will be analyzed by paired-sample *t*-test on the pre-surgical and 1-week and 6-months post-surgical results. The intervention effect on QST and CPM will be assessed with linear mixed-effects regression at the three time points.

Intervention effects on pain catastrophizing, anxiety, depression and fear of cancer recurrence at two months will be evaluated using the independent-samples *t*-test. With linear mixed-effects, regression differences in level and slope are compared between e-CBT and EDU taking all longitudinal measurements into account.

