## Introduction

### Background and rationale {6a}

Persistent pain after breast cancer treatment (PPBCT) is highly prevalent [1]. In the acute phase following surgery, reconstructive surgery, radiotherapy, and chemotherapy, up to 50% of the patients suffer from pain [2, 3]. In around 30% (15–65%) of patients, this pain persists for 1 year or longer. Previously, it was thought that pain after mastectomy was mainly neuropathic, caused by damage to the intercostal brachial nerve (ICBN). However, pain may also originate from other sources such as lymphedema, scarring of tissues of the chest wall [4], or from muscle guarding [5]. Once chronic, PPBCT and secondary problems are difficult to treat and require a complex individualized multidisciplinary approach [6, 7]. The standard pharmacological treatment of PPBCT consists of antidepressants [8, 9], and capsaicin [10], but even though effective, intolerable side effects often limit (long-term) treatment. Interventional treatment options of PPBCT target the thoracic dorsal root ganglia, intercostal nerves [11], stellate ganglion [12], thoracic sympathetic chain [13], and fascia of the thoracic wall [14].

In the past decade, research has identified treatment- and patient-related factors increasing the risk for PPBCT. Treatment-related risk factors such as axillary lymph node dissection, radiotherapy, and intercosto-brachial nerve handling may directly increase tissue damage. Patient-related risk factors such as genetic haplotypes, young age, high BMI, pre-existing pain, high postoperative pain intensity, and psychological distress suggest a greater vulnerability of the nociceptive system that is prone to sensitization [15–18]. Quantitative sensory testing (QST) demonstrated the presence of central sensitization in patients with PPBCT [19–22]. Moreover, there is accumulating evidence that patients with persistent postsurgical pain have less efficient inhibitory modulation of afferent nociceptive signals [23–26].

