#### Secondary study parameters/endpoints

Secondary outcomes of the study are pain intensity scores (intercept and slope) during the first postoperative week (NRS, pain diary), cessation of postoperative opioid use (no. of days), and PPBCT prevalence after 12 months. Mean PPBCT intensity in the operated area (NRS), presence of neuropathic pain (Doleur neuropathique (DN4)) [59], and pain interference (Brief Pain Inventory (BPI) [60], measured at 2, 6, and 12 months.

(Pain) sensitivity is assessed with quantitative sensory testing (QST) before and at 6 months post-surgery. QST is measured at the bilateral pre-axillary dermatomes Th 3. In patients with persistent postoperative pain in the operated area, the 6-month QST measurement is performed in the painful and the corresponding contralateral location. QST measurements are performed according to the protocol developed by the DFNS [61]. Conditioned pain modulation (CPM) is measured before, at 1 week postoperatively and 6 months later according to the suggestions of Yarnitsky et al. [62]. The chosen CPM algorithm compares three repetitions of pressure pain threshold measurements in the thenar contralateral to the operated side, before and immediately after a cold pressor test delivered to the other hand with ice water.

In addition the psychological parameters anxiety, fear of recurrence, catastrophizing, and depression are assessed together with the cancer related quality of life before and up until 12 months after surgery.

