### Assignment of interventions: allocation

#### Sequence generation {16a}

Allocation is performed using electronic stratified randomization with random permuted block sizes. Stratification factors are axillary dissection and center of inclusion.

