#### Primary study parameter(s)

Group differences concerning the prevalence of PPBCT at 6 months follow-up will be reported stratified by treatment allocation. Comparisons between e-CBT and EDU will be made using logistic regression analysis, adjusted for the variables used to stratify randomization. The odds ratio (OR) including 95% CI and *p*-value will be reported.

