## Trial status

The actual protocol version is V4-amendement-2/2022-02-21. Recruitment started in June 2021. To date, 130 patients have been recruited at six study sites in the Netherlands*. The first patient was included June 21, 2021. Planned termination of inclusion is June 2023.

*Study sites: Antoni van Leeuwenhoek Ziekenhuis – The Netherlands Cancer Institute, Amsterdam; Alexander Monro Breastcancer Hospital, Bilthoven; Reinier de Graaf Hospital, Delft; University Medical Center UMCG Groningen, Radboud University Medical Center, Nijmegen; Maastricht University Medical Center+ (MUMC+), Maastricht.

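### The opioid-cessation comparison names neither stratification by axillary dissection nor a between-arm estimate with an interval; adding both is a cheap gain on a secondary endpoint

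*Protocol article*

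**What the plan says.** The endpoint is listed under Secondary study parameters/endpoints as "cessation of postoperative opioid use (no. of days"). Its whole stated analysis, under Secondary study parameter(s) in the statistical methods, is: "Time to opioid cessation will be analyzed with the Kaplan-Meier method and compared using the log-rank test". No strata, covariates, hazard ratio, difference in medians or interval are mentioned.

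Three other places bear on this:

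- Sequence generation {16a}: "Stratification factors are axillary dissection and center of inclusion".
- Primary study parameter(s): "Comparisons between e-CBT and EDU will be made using logistic regression analysis, adjusted for the variables used to stratify randomization". The reported result begins "The odds ratio (OR) including 95% CI and" also includes a p-value.
- Background and rationale {6a}: "Treatment-related risk factors such as axillary lymph node dissection" are listed, with others, as possible causes of greater tissue damage.

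Trial status reports recruitment at six sites, so crossing the two stratification factors gives 2 x 6 = 12 cells.

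**The concern.** Stratified randomization balances the arms within each stratum. If the factor is prognostic, an analysis that ignores it pays in two ways. The pooled log-rank variance takes no credit for the enforced balance, so it is too large and the test is conservative. Pooling patients with different stopping rates also pulls the marginal arm effect towards the null. The primary analysis avoids this by adjusting; the opioid analysis, as described, does not.

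The second gap is in reporting. A log-rank test gives a p-value. Kaplan-Meier gives a curve and a median for each arm, but the text plans no contrast between arms with an interval. That matters here because the Background says an earlier one-session internet intervention before breast cancer surgery shortened opioid use without changing pain intensity. Setting a five-session programme against that result calls for a magnitude and its precision.

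**Working it through.** **Sample size taken from the plan.** The article sizes the trial only for the primary endpoint: 50% versus 25%, 80% power, alpha 0.05 (taken as two-sided). With the unpooled normal formula:

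n per arm = (1.960 + 0.842)² x (0.50 x 0.50 + 0.25 x 0.75) / 0.25² = 54.94, so 55.

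With 20% dropout, 110 / 0.8 = 137.5, so 138. Both figures reproduce. No power or effect size is given for opioid cessation, so 110 and 138 are used below simply as the available numbers.

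**Assumptions not in the documents.** Arm hazard ratio 1.6 or 1.7 (above 1 means faster cessation); dissection in 20-40% of patients; dissection multiplying the stopping rate by a stratum HR between 1.0 (no effect) and 0.33; follow-up for opioid use censored at day 60 in sets A and B.

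**Anchor.** By Schoenfeld's formula, power = Φ(|ln HR| x √(D/4) − 1.96), with D events. For HR 1.6 and D = 138: 0.470 x 5.874 − 1.96 = 0.80, power 78.8%. For HR 1.7 and D = 110: 0.531 x 5.244 − 1.96 = 0.82, power 79.5%. The simulated unstratified power with a non-prognostic stratum (77.9% and 78.3%) agrees with these.

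**Simulated power, unstratified → stratified by dissection.** Set A: N = 138, arm HR 1.6, 30% dissection, 5,000 runs. Set B: arm HR 1.7, 20-40% dissection, 2,000 runs (Monte Carlo standard error about 1 point). Set C: a separate run at the N, arm HR and prevalence of set A, given to the nearest whole percent.

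| Stratum HR | A (N=138) | B (N=110) | B (N=138) | C (N=138) |
|---|---|---|---|---|
| 1.0 | 77.9 → 77.0 | 78.3 → 77.3 | 85.9 → 85.2 | 78 → 76 |
| 0.7 | – | 74.5-75.2 → 75.0-75.3 | 84.0-85.7 → 84.8-86.6 | 75 → 75 |
| 0.5 | 69 → 76 | 70.4-72.4 → 75.6-78.6 | 79.8-82.0 → 85.3-86.4 | 70 → 76 |
| 0.33-0.35 | 62 → 75 | 60.2 → 75.3 | – | 61 → 75 |

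At stratum HR 0.5 the gains run from 85.4 − 82.0 = 3.4 points (B, N = 138, 20% dissection) to 76 − 69 = 7 points (A). At 0.33-0.35 they are 13 points (A), 14 (C) and 15 (B).

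**Type I error of the unstratified test.** About 5% when the stratum effect is nil or modest. At stratum HR 0.5 it is 4.1% in A and 3.5-5.0% in B. It is 3.4% in A at 0.35 and 2.6-2.8% in B at 0.33. It is at or below nominal within simulation error.

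**Stratifying by all 12 cells.** With 138 patients the average cell holds 138 / 12 = 11.5. Against the unstratified test in B, power changes by 69.2 − 78.3 = −9.1 points at stratum HR 1.0 (N = 110) and by 80.6 − 84.0 = −3.4 at 0.7 (N = 138, 20% dissection). At 0.5 the change is roughly −3 to +1 points. It gains only at 0.33: 67.8 − 60.2 = +7.6. These runs mostly assume that center has no effect on stopping. In the one setting with a center effect (standard deviation 0.3 on the log hazard; N = 110, stratum HR 0.5), power was 69.4% unstratified, 73.3% by dissection and 70.2% by 12 cells, so dissection alone was still best.

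**The case against.** The strongest reply is that the article says the log-rank test and never calls it unstratified. An article condenses a longer document, and strata or a Cox model may stand in a full protocol or SAP not shown. The t-tests and mixed models in the same section name no adjustment or interval either. This stands as a limit on the point: the text is silent, and the concern is about what it fixes so far. It does not remove the point, because the adjacent paragraph on the primary outcome does state both adjustment and an interval, so the plain reading is an ordinary log-rank test.

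A second reply is that the trial has two stratification factors, so stratifying by only one abandons the rule that analysis follows design. That is fair as a matter of principle. Leaving center out is a practical choice that rests on the small cells, not a correction of an error.

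A reader might also infer stronger things that the documents do not support:

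- That the test is invalid. Its type I error is at or below nominal.
- That power is certainly lost. This needs dissection to predict opioid duration strongly. The Background links it to persistent pain, no passage links it to days of opioid use, and at stratum HR 0.7 there is essentially no difference.
- That dissection was chosen as a stratum because it causes pain. The section on sequence generation gives no reason for either factor.
- That no effect information is produced, or that a null result could not be interpreted. Curves and medians by arm are available; a null result would only be harder to interpret without an interval.
- That power promised for this endpoint is being wasted. None is promised.

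**Conclusion.** The point holds as an improvement in efficiency and reporting on a secondary endpoint, not as an error that invalidates it. Its two parts differ in certainty. The absence of a planned between-arm estimate with an interval stands however prognostic dissection is. The power argument is conditional on the stratum effect, and the size of the gain also depends on the assumed arm hazard ratios of 1.6 to 1.7. The case for stratifying rests on an uneven trade: about 1 point lost if dissection is irrelevant (0.7 to 1.0 in sets A and B, 2 in the rounded figures of set C), against several points gained if it is strongly prognostic.

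**What to change.** State that time to opioid cessation will be compared with a log-rank test stratified by axillary dissection as recorded at randomization. Report the hazard ratio with 95% CI from a Cox model stratified by the same factor, so that estimate and test rest on the same comparison within strata. Keep the Kaplan-Meier curves and medians by arm. Do not stratify by all 12 dissection-by-center cells, and say in the plan why center is left out. If the full protocol or SAP already specifies this, the article needs only to be brought into line.

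The change is one line and needs no new data, since dissection is already recorded for randomization. It should be fixed before the arms are compared.

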#### Other study parameters

Other parameters including clinical and psychosocial patient characteristics, breast-cancer treatment related variables, and compliance with the psychological intervention are assessed at the time points shown in Table 2.

**Table 2 Tab2:** Parameters and assessment time points

Parameters	Instrument	T 0	T1	T2	T3	T4
Pain operated breast	NRS	x	x	x	x	x
	Pain localization	x		x	x	x
	BPI [60]	x		x	x	x
	DN4 [59]	x	x	x	x	x
Pain unrelated to BC treatment elsewhere	NRS	x		x	x	x
	Localization	x		x	x	x
Shoulder function	DASH [63]	x			x	x
Pain sensitivity	CPM	x	x		x	
	QST	x			x	
Pain catastrophizing	PCS [54]	x		x	x	x
Anxiety	HADS-A [52]	x		x	x	x
Depression	PROMIS short form v1.0 [64, 65]	x		x	x	x
Quality of life	EORTC-QLQ C30+BC [66]	x			x	x
Surgical fear	SFQ [67] & single item [16]	x				
Fear of recurrence	CARS [68]	x		x	x	x
Breast cancer characteristics	TNM, receptors, histological profile	x			x	
	non-related chronic pain complaints	x			x	x
	pain medication	x	x	x	x	x
	Sedative and antidepressive medication	x	x	x	x	x
Patient characteristics	BMI	x			x	x
	Comorbidity and intoxications	x				x
	Unspecific symptoms	x		x	x	x
Breast cancer treatment details	Type of surgery		x	x	x	x
	ICBN handling		x			
	Breast cancer treatment complications		x	x	x	x
	Radiotherapy			x	x	x
	Chemotherapy	x		x	x	x
	Hormonal therapy	x		x	x	x
Anesthesia	Perioperative regional techniques		x			
	Acute pain day 0–7		x			
Patient compliance with protocol				x		

*T0* 1–3 weeks pre-surgery, *T1* postoperative week, *T2* 2 months follow-up, *T3* 6 months follow-up, *T4* 12 months follow-up. *NRS* numerical rating scale (0=no pain, 10=maximum pain), *BPI* brief pain inventory, *DN4* doleur neuropathique 4 questions, *CPM* conditioned pain modulation, *QST* quantitative sensory testing, *PCS* pain catastrophizing scale, *HADS* hospital anxiety and depression scale, *PROMIS* patient-reported outcomes measurement information system, *EORTC-QLQ* European Organization for Research and Treatment of Cancer Quality of Life Questionnaire, *SFQ* surgical fear questionnaire, *CARS* fear of cancer recurrence scale, *DASH* disability of the arm, shoulder and hand questionnaire, *BMI* body mass index, *ICBN* intercostobrachial nerve

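### Quality of life at 6 and 12 months is tested only by an unadjusted t-test although it is measured at T0; the stated 2-month psychological contrasts share the weakness in part

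*Protocol article*

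**What the plan says.** Three statements in the protocol article matter here.

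- **Quality of life.** Under Secondary study parameter(s): "Quality of life at 6 and 12 months will be compared between groups using the independent-samples" t-test. No covariate is named and no other model is given for this outcome.
- **Psychological scales.** The same section says: "Intervention effects on pain catastrophizing, anxiety, depression and fear of cancer recurrence at two months will be evaluated using the independent-samples" t-test. The next sentence adds a linear mixed-effects analysis in which "regression differences in level and slope are compared between e-CBT and EDU taking all longitudinal measurements into account". This model covers the four psychological scales and not quality of life.
- **Baseline data.** Under Secondary study parameters/endpoints, the psychological measures "are assessed together with the cancer related quality of life before and up until 12 months after surgery". Table 2 agrees. The quality-of-life questionnaire ("EORTC-QLQ C30+BC [66"]) is marked at T0, T3 and T4. PCS, HADS-A, PROMIS depression and CARS are marked at T0, T2, T3 and T4. T0 is "1–3 weeks pre-surgery".

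For contrast, the primary analysis is a logistic regression adjusted for the stratification variables, which Sequence generation gives as axillary dissection and center.

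**The concern.** An independent-samples t-test takes no covariate. Naming it therefore excludes both the T0 score and the stratification factors; it does not leave them to be settled in an SAP. With a continuous scale that was measured before treatment, the T0 score is usually the strongest available predictor of the follow-up score. Leaving it out has two consequences:

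- The standard error is larger than it needs to be.
- If the arms happen to differ at T0, part of that difference carries through to the follow-up contrast. Randomization is not stratified on any of these scores, so nothing in the design limits such a difference.

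For quality of life the plan offers no second analysis that could recover the information. For the psychological scales it offers one, but leaves open how the two relate. Anxiety and catastrophizing at 2 months are the targets of e-CBT soon after the last session. If the t-test and the mixed model disagree there, the plan does not say which is the result.

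**Working it through.** **Inputs from the protocol article (Sample size).** Prevalence 50% versus 25%, alpha 0.05, power 80%, 55 per group, 20% drop-out, 138 randomized. Sidedness is not stated; two-sided is assumed.

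**Assumptions, not in the document.** The correlation r between the T0 and follow-up score is taken as 0.3 to 0.7, and the treatment effect as 0.4 SD. The article states no power target for these outcomes.

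**Step 1: the plan's own figure.** With the unpooled two-proportion formula,

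n = (1.960 + 0.842)² × (0.50 × 0.50 + 0.25 × 0.75) / 0.25² = 54.9, so 55 per group.

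110 / 0.80 = 137.5, so 138. Both figures reproduce, and 55 analysed per arm is the natural basis for what follows.

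**Step 2: effect of adjusting for T0.** ANCOVA multiplies the residual variance by 1 − r². The standardized effect becomes 0.4 / √(1 − r²), and the noncentrality of the two-sample t statistic is that value times √(55/2). The t-test would need 55 / (1 − r²) patients per arm to match. The few degrees of freedom spent on covariates are ignored.

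| r | 1 − r² | Effective effect (SD) | Noncentrality | Power | t-test n per arm to match |
|---|---|---|---|---|---|
| none (t-test) | 1.00 | 0.400 | 2.10 | 55% | 55 |
| 0.3 | 0.91 | 0.419 | 2.20 | 59% | about 60 |
| 0.5 | 0.75 | 0.462 | 2.42 | 67% | about 73 |
| 0.6 | 0.64 | 0.500 | 2.62 | 74% | about 86 |
| 0.7 | 0.51 | 0.560 | 2.94 | 83% | about 108 |

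The residual variance falls by 9% at r = 0.3 and by 49% at r = 0.7. The difference detectable with 80% power (normal approximation) is (1.960 + 0.842) × √(2/55) = 0.534 SD for the t-test. It falls to 0.510, 0.463 and 0.382 SD at r = 0.3, 0.5 and 0.7.

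**Step 3: simulation check.** With a 0.5 SD effect, 55 per arm and 10,000 runs per setting, the t-test had 73–75% power. ANCOVA had 78%, 85% and 95% at r = 0.3, 0.5 and 0.7. The Step 2 formula gives 74% for the t-test and 78%, 85% and 95% for ANCOVA.

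**Step 4: chance imbalance.** The T0 difference between arms has standard deviation √(2/55) = 0.19 SD units, so its 95% range is ±0.37. Given an imbalance at that limit, the unadjusted follow-up contrast shifts by r × 0.37, which is 0.11, 0.19 and 0.26 SD at r = 0.3, 0.5 and 0.7.

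**Step 5: which outcomes this reaches.** For quality of life, Steps 2 and 4 apply in full, because the t-test is the only analysis. For the four psychological scales they apply to the stated 2-month t-test. The mixed model may carry T0 as one of its measurements, in which case a T0 difference can be absorbed by the intercept. Its stated targets, however, are level and slope, not the 2-month difference given T0.

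**The case against.** **The mixed model already deals with the psychological scales.** This is the strongest objection, and it stands in part. A reader might infer from the t-test sentence alone that chance imbalance goes uncorrected for all five constructs, or that a negative 2-month result would rest on that test alone. The sentence that follows it does not support this: all longitudinal measurements plausibly include T0. What remains is that the model is not specified as a baseline-adjusted 2-month contrast, and that no order is set between it and the t-test.

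**The t-test is valid.** This stands. Under randomization it is unbiased on average and keeps its type I error. Ignoring stratification factors generally makes it slightly conservative; no figure is put on that here. The shift in Step 4 is conditional on an observed imbalance and is not a systematic bias.

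**The gain may be small.** This stands as a caution. Entry to the randomized part requires a high score on HADS-A, CARS, PCS or the surgical fear item, which may restrict range and lower r for the first three. T0 also falls shortly before surgery, and follow-up comes after surgery and possibly adjuvant treatment. Both point towards the lower end of the range. However, any one criterion suffices for entry, so no single scale is cut off for everyone, and neither depression nor quality of life is an entry criterion.

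**A condensed article leaves detail to the SAP.** This excuses silence about covariates in the mixed model. It does not excuse the t-tests, because there the method is named.

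**Conclusion.** The point holds in full for quality of life at 6 and 12 months. A named unadjusted test passes over a baseline that is already collected, and no other analysis uses it. For the four psychological scales it holds only in reduced form: the stated 2-month test is unadjusted, and its standing relative to the mixed model is undefined.

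The size depends on assumed values. At 55 per arm and 0.4 SD, the gain runs from 4 percentage points of power (55% to 59% at r = 0.3) to 28 points (55% to 83% at r = 0.7). The textual facts are certain; the gain is not. This is a free improvement to secondary outcomes. Nothing here touches type I error, the primary logistic regression or the sample size.

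**What to change.** - **Quality of life.** Replace the two t-tests by ANCOVA of the follow-up score on arm, the T0 value of the same scale, axillary dissection and center. A longitudinal model of the 6- and 12-month scores with these covariates, reporting the arm difference at each visit, serves equally well.
- **Psychological scales.** Drop the separate 2-month t-tests. For each scale, fit one longitudinal model to the 2-, 6- and 12-month scores, with the T0 score and the stratification factors as covariates and an arm-by-visit term. Report its 2-month contrast as the 2-month result. If the level-and-slope comparison is kept, state that it is supplementary.

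The cost is a change of wording in the statistical methods, ideally before unblinded outcome data are seen. No new data, visits or patients are needed.

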## Interventions

### Explanation for the choice of comparators {6b}

To provide a control group with comparable intervention conditions to the e-CBT group, an online educational (sham) intervention is composed. Women randomized to this EDU group receive an intervention based on information about surgery, communication skills, and a healthy lifestyle. Content referring to psychosocial support is avoided. The number of online sessions and appointments with a therapist are equal to the e-CBT intervention.

Women with low to normal levels of anxiety and catastrophizing are allocated to the non-randomized control group receiving TAU. This group serves as reference group for the primary outcome PPCBT and for the QST/CPM measurements.

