### Relevant concomitant care permitted or prohibited during the trial {11d}

AMAZONE does not interfere with the planned oncological treatment nor prohibits any other necessary medical, psychological, or psychiatric treatment. In case additional psychological or psychiatric treatment is initiated during the 2 months after surgery in the randomized groups, a sensitivity analysis will be applied to assess potential confounding by this subgroup.

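### At 6 months the paired t-test of QST and CPM measures change from all causes since before surgery, so it should not be labelled the effect of surgery

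*Protocol article*

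**What the plan says.** Under Secondary study parameter(s) the Protocol article fixes both the quantity and the test: "The effect of surgery on QST and CPM parameters will be analyzed by paired-sample" *t*-tests, with the pre-surgical result set against the 1-week and 6-month results. It names no comparator and no adjustment. The next sentence gives the e-CBT effect on the same measures its own between-group mixed model.

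Other sections bear on what this test can show:

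- **Timing.** Under Secondary study parameters/endpoints, QST is scheduled before surgery and at 6 months only. CPM "is measured before, at 1 week postoperatively and 6 months later". Table 2 agrees.
- **Test site.** "QST is measured at the bilateral pre-axillary dermatomes Th 3", but in patients with persistent pain in the operated area "the 6-month QST measurement is performed in the painful and the corresponding contralateral location".
- **Other treatment.** Section {11d}: "AMAZONE does not interfere with the planned oncological treatment nor prohibits any other necessary medical, psychological, or psychiatric treatment". Table 2 records radiotherapy from T2 onwards, and chemotherapy and hormonal therapy at T0 and again from T2.
- **Radiotherapy as a cause in its own right.** Section {6a}: "Treatment-related risk factors such as axillary lymph node dissection, radiotherapy, and intercosto-brachial nerve handling may directly increase tissue damage".
- **Groups.** The opening of Statistical methods {20a} presents the techniques as those for the two randomized groups, with exploratory comparisons against the low-fear group by similar methods. Of TAU, section {6b} says: "This group serves as reference group for the primary outcome PPCBT and for the QST/CPM measurements".

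**The concern.** A within-patient test before and after an event has no control. It shows whether the mean has moved, not why. The protocol itself places several other possible causes inside the 6-month interval. One of them, radiotherapy, it names as a source of tissue damage. Another, e-CBT, it hopes will change these very measures, since Objectives {7} lists an e-CBT effect on nociceptive transmission and central pain inhibition.

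If the label stands, a 6-month shift in sensory thresholds or CPM will be published as something surgery did, although the data would fit adjuvant treatment, retest drift or the study intervention equally well. Pooling the randomized arms would also mix part of any e-CBT effect into the reported surgical change, or cancel part of a real one.

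**Working it through.** The plan gives no sample size, effect size or power for this test, so there is no figure to reproduce. The check sets the calendar against the label and then illustrates the size.

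**1. What lies between the two measurements**

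| Possible cause | T0 to 1 week (CPM only) | T0 to 6 months (QST and CPM) |
|---|---|---|
| Surgery | yes | yes |
| Radiotherapy | not recorded before T2 | yes (T2, T3) |
| Chemotherapy, hormonal therapy | only if under way at T0 | yes (T0, T2, T3) |
| e-CBT (one arm) | session 1; session 2 falls due at day 7 | all five sessions (to day 28) |
| Retest drift | yes | yes |
| Change of QST site | not applicable | yes, in patients with pain |

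Sources: Table 1, Table 2 and Secondary study parameters/endpoints.

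**2. What the paired test estimates**

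Write the mean change as S + A + R + I: surgery, adjuvant treatment, retest drift and study intervention. The test asks whether the sum is zero, whereas the label claims that it asks whether S is zero. At 6 months A, R and, in the e-CBT arm, I can all be non-zero. At 1 week A and I are small by schedule, though R remains.

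**3. Effect of pooling the randomized arms**

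The article does not say whether the arms are pooled. If they are, at the planned 55 per group, and e-CBT shifts the change by δ relative to EDU:

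pooled change = (55 × EDU change + 55 × (EDU change + δ)) / 110 = EDU change + δ/2.

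Half of any e-CBT effect would be counted as surgery.

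**4. Size, under stated assumptions**

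Assume S = 0 and let all other influences shift the paired difference by d standard deviations. The probability of p < 0.05 (two-sided) comes from the noncentral t distribution with n − 1 degrees of freedom and noncentrality d√n. For n = 110 and d = 0.2 the noncentrality is 0.2 × √110 = 2.10.

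| n | d = 0.1 | d = 0.2 | d = 0.3 |
|---|---|---|---|
| 50 | 0.11 | 0.28 | 0.55 |
| 110 | 0.18 | 0.55 | 0.88 |
| 138 | 0.22 | 0.65 | 0.94 |

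The nominal rate is 0.05. Here 138 is the planned randomized total, 110 is two groups of 55, and 50 is roughly one arm. The values of d, and the number of patients with QST and CPM data, are assumptions.

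**5. What the contralateral site can do**

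The operated-minus-contralateral difference removes whatever affects both sides alike, such as drift or a systemic drug effect. It also removes any bilateral or central part of S, and it keeps anything confined to the operated side, which may include radiotherapy. In patients with pain, both 6-month sites move together away from Th3. The side difference is then better protected than the raw change, but it still compares different places.

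**The case against.** The strongest reply is that little hangs on this test. Objectives {7} lists effects of e-CBT, not of surgery. In the background section, the mechanisms that QST and CPM are meant to unravel are those of e-CBT, and the mixed model between groups serves that aim. This stands, and it is why the point is minor.

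Second, the reply may be that which groups enter and what is adjusted for is detail for an analysis plan not shown here. That is fair for covariates. It does not answer the point: the article itself names the quantity, and no covariate list turns an uncontrolled pre-post change into an effect of surgery.

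Third, controls are not wholly absent: TAU is the named reference for QST and CPM, and exploratory comparisons of pain sensitivity with it are planned. Those comparisons are between groups that all had surgery, so they do not isolate what surgery did within patients.

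A reader might go further and infer three things that the documents do not support:

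- *That every change will be wrongly attributed.* The 1-week CPM test comes before radiotherapy is first recorded and before most of e-CBT. At 6 months surgery remains one possible cause; it just cannot be told apart from the others.
- *That near-certain false positives follow from testing several hundred patients.* That needs all three groups pooled and every patient tested. The methods are described for the two randomized groups, and section {18a} speaks of the centers that assess QST and CPM, which may be a subset.
- *That the side-to-side difference should replace the raw change.* It would discard the central sensitization that the background stresses, and the Th3 pair may not be repeated in patients with pain.

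**Conclusion.** The concern holds for the 6-month QST and CPM tests. They estimate change from all causes since before surgery, and the protocol's own text supplies several of those causes. As QST has no 1-week measurement, every QST result reported under this label is affected. For 1-week CPM the label is tolerable with caution, because session 1 of e-CBT, systemic therapy already under way at T0 and retest drift remain.

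Severity is minor. The primary endpoint is untouched, and so is the randomized comparison of e-CBT with EDU on QST and CPM. The size cannot be fixed from the documents. The 55% at n = 110 and 0.2 SD only illustrates that a modest non-surgical shift would often be declared significant; at 0.1 SD it is 18%.

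**What to change.** In Secondary study parameter(s):

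1. Call the 6-month result *change from before surgery to 6 months*. Keep *effect of surgery*, with caution, for 1-week CPM only, and make clear that the 1-week comparison does not apply to QST.
2. Run the paired test separately in TAU, EDU and e-CBT. Do not pool e-CBT. Read any surgical change from the groups without e-CBT, noting that TAU was selected for low anxiety and catastrophizing.
3. For QST, report the change in the operated-minus-contralateral difference beside the raw operated-side change, not in its place.
4. Flag or separate patients whose 6-month QST site was moved to the painful location.
5. Treat any split by radiotherapy as descriptive, since radiotherapy is not randomized.

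This adds no visit or measurement. The cost is fewer patients per test and a more modest conclusion.
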